### Randomization

Before enrolling the first study participant, a research statistician generated the balanced randomization scheme for treatment allocation at both clinical sites using the R Statistical Package.^21^ This method randomly assigns participants to one of three intervention groups (*N* = 20 per group): 1) tAIH + WALK_tSTIM_, 2) tAIH + WALK_tSHAM_, and 3) Placebo + WALK_tSTIM_ in blocks of 6 participants. Using this scheme, the site coordinator will assign each participant to their respective intervention group in the order in which they complete the walking practice sessions. Although the coordinator informs participants about their possible group assignment, they will be blinded to the treatment they receive (i.e., tAIH or Placebo, WALK_tSTIM_, or WALK_tSHAM_). The clinical raters and trainers will also be unaware of each participant's treatment assignment. Based upon reports from participants blinded during our previous tAIH study,^6^ >75% guessed incorrectly or were uncertain of the breathing intervention received, suggesting that our previous blinding and air delivery methods were effective.

We plan a similar integrity analysis for the stimulation sham protocols (no stimulation). Participants guess the interventions received at the end of each treatment session and indicate their guess confidence using a Likert scale.^22,23^ Using a contingency table and Fisher's exact test, we will determine whether the probability of correct guessing differs from chance.

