#### Cognitive ability

We will assess cognitive function after the last walking practice session and after the last intervention session (T_0_, T_2_; Fig. 3).^48^ The California Verbal Learning Test, Third Edition (CVLT3) brief form will quantify verbal learning and memory.^49^ We also assess executive function with the Oral Trail Making Test (O-TMT).^50^ These tests examine the areas of cognitive ability most likely to be affected by an excessive dose of low oxygen, such as during severe sleep apnea.^51^

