Daily tAIH priming enhances the potency of WALK_tSTIM_ on improving walking speed in people with chronic SCI. We quantify potency as the number of tAIH + WALK_tSTIM_ sessions (eight total) needed to achieve the MCID in walking speed.^57^ We assess walking speed with the 10MWT at the end of each training session and predict that those who receive tAIH + WALK_tSTIM_ will achieve an MCID with fewer training sessions than either treatment alone (Placebo + WALK_tSTIM_ or tAIH + WALK_tSHAM_). To test this hypothesis, we will use linear mixed models with number of sessions to achieve the MCID as the outcome with treatment group and 10MWT speed at baseline as fixed effects and participant as the random effect. We anticipate that improvement in walking recovery also will correlate with improved 6MWT, TUG, SCI-FAI, WISCI II, and LEMS scores, suggesting the clinical relevance of this intervention across impairment levels and walking deficits.

#### Hypothesis 3

Daily tAIH+WALK_tSTIM_ does not induce maladaptive changes (spasticity, pain, systemic hypertension, and AD) in persons with chronic SCI. We predict no difference in SCATS, NPRS, CVLT, O-TMT, NBDS, and NBSS scores after daily tAIH + WALK_tSTIM_ compared to baseline. We will use a Friedman two-way repeated-measures ANOVA by ranks to compare these relative scores between and within groups. Changes in these scores relative to baseline are the repeated measures. Intervention (tAIH + WALK_tSTIM_, Placebo + WALK_tSTIM_, and tAIH + WALK_tSHAM_) and time are the fixed main effects, with subject as the random effect. We also predict that tAIH + WALK_tSTIM_ will not elicit a greater incidence of systemic hypertension or AD in persons with chronic SCI.

To test these subhypotheses, we will compare the incidence rates of these maladaptive changes between interventions using the relative risk.^58,59^ A relative risk of 1 will indicate no association between the maladaptive measures and interventions. Using the 95% confidence interval of the relative risk,^59^ we will determine whether there is a statistically significant association between interventions. We predict that the relative risk of hypertension and AD are not different between tAIH versus placebo interventions and WALK_tSTIM_ versus WALK_tSHAM_ interventions.

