To minimize biases and errors in data collection, a designated lead physical therapist, blinded to study interventions, ensures participant adherence to the protocol and consistent scoring among therapists by regularly checking all assessment logs for adherence to standard clinical procedures. Non-blinded research staff members (including post-doctoral fellows, lab engineers, and research assistants) assist clinicians with training setup and clinical data collection. The study principal investigator oversees all study procedures and ensures the correct collection and documentation of data. If participants miss more than two walking practice sessions or intervention sessions, we will not conduct further assessments and exclude their data from analyses. However, if participants miss an assessment session, we record their data as “missing” at that time point.

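### Hypothesis 3 names a Friedman test for a comparison between three parallel arms, which that test cannot make

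*Protocol article*

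**What the plan says.** All of this is in the protocol article; the statistical analysis plan is not at hand.

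- **Claim under test** (Statistical analysis, Hypothesis 3): "Daily tAIH+WALK_tSTIM_ does not induce maladaptive changes". For the scores, the expectation is: "We predict no difference in SCATS, NPRS, CVLT, O-TMT, NBDS, and NBSS scores after daily tAIH" plus WALK_tSTIM, relative to baseline.
- **Method** (same place): "We will use a Friedman two-way repeated-measures ANOVA by ranks to compare these relative scores between and within groups". On the data it says: "Changes in these scores relative to baseline are the repeated measures". On the effects, it lists intervention "and time are the fixed main effects, with subject as the random effect".
- **Design** (Randomization): "This method randomly assigns participants to one of three intervention groups". Intervention therefore varies between participants and never within one.
- **Timing of cognition** (Cognitive ability): "We will assess cognitive function after the last walking practice session and after the last intervention session", that is, at T0 and T2. The other four scores are taken at baseline and at the testing and follow-up visits (Table 2).
- **Missed visits** (last paragraph of Statistical analysis): "However, if participants miss an assessment session, we record their data as" missing at that time point.
- **Other safety outcomes** (Hypothesis 3): hypertension and autonomic dysreflexia have their own between-arm comparison, a relative risk with a 95% confidence interval.

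**The concern.** The two ways in a Friedman analysis are the block and one factor that varies within the block. With participant as the block, that factor is visit. Arm is constant within a participant, so it is neither of the two ways, and the test has no fixed effect for arm and no random-effect structure. The sentence naming the test and the sentence listing its effects therefore describe different analyses, and the named one cannot make the first of the two comparisons it is assigned.

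Safety is Aim 3 of the trial. The value of randomised controls for these scores is that they separate an effect of the combination from changes that would occur with either component, with training, or with repeated testing. If the only named analysis cannot use the controls, that separation is lost. It matters most for cognition, because the article itself says that it chose these tests for the abilities most likely to suffer from too much low oxygen.

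**Working it through.** The plan gives no figure for Hypothesis 3; its sample-size section covers Aims 1 and 2 only. The check is therefore of the test's structure, followed by a simulation.

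**1. Ranks carry no information on arm.** Changes from baseline at T0, T1, T2, F1, F4 and F8 give k = 6 values per participant. Ranked within participant and without ties, they sum to k(k + 1)/2 = 6 × 7/2 = 21 for everyone, in every arm. A participant who is worse at all six visits has the same rank total as one who is better at all six. Subtracting a participant's own baseline does not change the ranks either.

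**2. Invariance.** Data were simulated for 48 participants (three arms of 16, the planned completers) with six values each. Before any shift, chi-square = 9.2857 and p = 0.0982. After adding 100 to every value in one arm, both were identical.

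**3. Rejection rates at 0.05.** Assumptions: 16 per arm, six visits, participant SD 1, residual SD 1, 4,000 runs, and one arm shifted by the same amount at every visit. The comparator is Kruskal-Wallis across arms on participant means.

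| Shift in one arm (residual SD) | Friedman, all 48 | Kruskal-Wallis |
|---|---|---|
| 0 | 4.8% | 4.6% |
| 1 | 4.7% | 72% |
| 2 | 4.4% | 100% |
| 5 | 4.8% | 100% |

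The Kruskal-Wallis rates depend on the assumed SDs. The flat Friedman column does not; it follows from step 1.

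**4. What the test does respond to.** Over all 48, a rise of 1 SD across visits shared by all arms was detected in 99% of runs, although the arms did not differ. Trends of +2 SD in one arm and −2 SD in another, a large difference between arms, were detected in 1.4%. The result thus reflects the average time course and not the contrast between arms.

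**5. Cognition.** CVLT3 and O-TMT are taken at T0 and T2, which gives one change per participant, so k = 1. The statistic is 12/[nk(k + 1)] × ΣR² − 3n(k + 1), where R is the rank sum at a visit. With k = 1 every rank is 1 and R = n, so it equals 12n²/(2n) − 6n = 0 on k − 1 = 0 degrees of freedom. There is no test. With the raw T0 and T2 scores instead, k = 2 and the procedure is equivalent to a sign test of T2 against T0, which is a comparison within participants only.

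**The case against.** **The prediction is about change from baseline, and Friedman within the combination arm addresses change.** This largely stands. If worsening is confined to the combination arm and begins after T0, then under the same assumptions Friedman within that arm rejects in about 66% of runs at 1 SD and 99.9% at 2 SD. Over all 48 participants it still rejects in about 20% and 55%. A reader might infer that harm in the combination arm would go untested. The documents do not support that, because the planned comparison within groups would examine it. The constant shift in the table is also not a realistic pattern of harm, since it is present at T0, before the combination starts; it only demonstrates the invariance. What is lost is attribution against the controls.

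**The authors may have meant a rank-based factorial or mixed analysis.** The effects listed beside the test suggest this. But then the label and the description contradict each other, and the text needs correction either way. A fuller analysis plan could add detail, but the article does not leave the method open: it names one that does not fit the design.

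**CVLT3 and O-TMT could be analysed on raw scores.** True, and the test is then defined. The article, however, specifies changes as the repeated measures.

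**Two further inferences go too far.** One is that missed visits would cost a definite share of participants. Friedman does need complete blocks, but the article gives no rate of missed visits, and handling incomplete blocks is commonly left to the analysis plan. The other is that a non-significant result will be reported as proof of safety. The article predicts no difference but does not say that.

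**Conclusion.** The point holds in this form: the named test cannot deliver the between-arm comparison promised for SCATS, NPRS, CVLT, O-TMT, NBDS and NBSS, and it does not contain the effects listed beside it. With participant as block, its sensitivity to a constant difference between arms is no more than its false-positive rate, whatever the size of the difference. This rests on the parallel design and on the structure of the test, not on assumed variances. On the change scores specified, the test cannot be computed at all for the two cognitive measures.

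The limits are equally clear. Friedman remains valid for change over visits within an arm, and worsening in the combination arm can be detected that way. The relative-risk comparisons for hypertension and autonomic dysreflexia, adverse event recording, and the walking analyses of Hypotheses 1 and 2 stand apart from this point. It is an error in a stated method that should be corrected before unblinding; it does not show that the safety aim as a whole fails.

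**What to change.** 1. Restrict Friedman, if it is kept, to change over visits within each arm, and remove the statement that it contains intervention as a fixed effect and subject as a random effect.
2. For the comparison between arms of SCATS, NPRS, NBDS and NBSS, name one analysis. Either use a rank-based or ordinal longitudinal analysis with arm, visit and arm-by-visit terms that accepts missed visits, or use rank ANCOVA of the score at a named visit on the pre-treatment score.
3. For CVLT3 and O-TMT, use rank ANCOVA of the T2 score on the T0 score, with arm as the factor.
4. Report the combination against each control with 95% confidence intervals, and base the safety statement on those intervals rather than on p of 0.05 or more alone.

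No new data or visits are needed. The cost is a revised paragraph and slightly more analysis work. The safety conclusion may also have to state how much worsening the data do not exclude, since the trial was sized for Aims 1 and 2. Worsening limits set in advance for each scale, or one particular ordinal model, are options that this correction does not require.

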### Outcome measures

We provide a summary of primary and secondary outcome measures in Table 2.

**Table 2. tb2:** Frequency of Clinical Assessments and Outcome Measurements

Measurement	Data collected	Time collected
Functional assessments		
Demographics	Age, sex, ethnicity, race, education	S
Medical history	SCI characteristics, medical records	S
Sleep quality^26^	Apnea-hypopnea rate	S
Medications	Name, dose, duration, and purpose	S, B, T, F
10-Meter Walk Test^71^	Time (s)	B, I, T, F
6-Minute Walk Test^72^	Distance (m)	B, T, F
Timed Up and Go Test^73^	Time (s)	B, T, F
WISCI II^74^	Scalar score (0–20)	B, T, F
SCI-FAI^41^	Scalar score (0–39)	B, T, F
Physiological assessments		
ISNCSCI exam^69,a^	SCI classification grade (A–E)	S
LEMS^42^	Scalar score (0–50)	B, T, F
SCATS^75^	Scalar score (0–18)	B, T, F
NPRS^43,44^	Scalar score (0–10)	B, T, F
NBDS^54^	Scalar score (0–47)	B, T, F
NBSS^55^	Scalar score (0–78)	B, T, F
Cardiovascular measures	Blood pressure, heart rate, SpO_2_, respiratory rate	B, I, T, F
Neurocognitive assessments		
MMSE^25^	Memory score (0–30)	S
CVLT3^49^	Total recall index score (40–160)	T
O-TMT^50^	Duration (s)	T

S = screening day; B = baseline; T = testing session; F = follow-up (1, 4, and 8 weeks); I = intervention day.

^a^
If no current/recent record of ISNCSCI exam is available.

CVLT3, California Verbal Learning Test, Third Edition; ISNCSCI, International Standards for Neurological Classification of Spinal Cord Injury; LEMS, lower extremity motor score; MMSE, Mini-Mental State Examination; NBDS, Neurogenic Bowel Dysfunction Score; NBSS, Neurogenic Bladder Symptom Score; NPRS, Numeric Pain Rating Scale; O-TMT, Oral Trail Making Test; SCATS, SCI Assessment Tool for Spastic Reflexes; SCI, spinal cord injury; SCI-FAI, SCI Functional Ambulation Inventory; WISCI, Walking Index for Spinal Cord Injury.

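### Hypothesis 3 analyses CVLT3 and O-TMT as repeated changes from baseline, but neither test is given at baseline and only one change per person, from T0 to T2, can be formed

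*Protocol article*

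**What the plan says.** Under Statistical analysis, Hypothesis 3, the protocol article makes one prediction for six scores: "We predict no difference in SCATS, NPRS, CVLT, O-TMT, NBDS, and NBSS scores after daily tAIH + WALK_tSTIM_ compared to baseline". The method follows: "We will use a Friedman two-way repeated-measures ANOVA by ranks to compare these relative scores between and within groups". The analysis variable is then fixed: "Changes in these scores relative to baseline are the repeated measures". Intervention and time are named as the fixed effects and subject as the random effect.

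The schedule for the two cognitive tests is given in two places. The Cognitive ability section says: "We will assess cognitive function after the last walking practice session and after the last intervention session (T_0_, T_2_; Fig. 3". Table 2 lists CVLT3 as "Total recall index score (40–160) T", and O-TMT also carries the single code T. In the table legend B, T and F are three different codes, for baseline, testing session and follow-up. The caption of Figure 3 likewise lists BL as an assessment distinct from T0, T1 and T2, which fall at the end of intervention weeks 2, 3 and 4.

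**The concern.** The analysis needs a quantity that the schedule does not produce. If no cognitive test is done at BL, there is no change from BL to rank, and whoever runs the analysis must choose another reference point and another method once data exist. The cognitive tests were selected because they cover abilities "most likely to be affected by an excessive dose of low oxygen", so they bear directly on the safety of tAIH. Table 2 offers no substitute: the MMSE is given at screening only and is not among the Hypothesis 3 scores. At stake is whether the reference visit, the test and the contrast for this part of the safety aim are fixed in advance or improvised.

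**Working it through.** The point concerns the schedule. The plan states no sample size, power or alpha figure for it, so there is no stated figure to reproduce.

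**Inputs**
- Visit codes (Table 2 legend and Figure 3 caption): B = BL; T = T0, T1, T2; F = F1, F4, F8.
- SCATS, NPRS, NBDS and NBSS (Table 2): B, T, F.
- CVLT3 and O-TMT (Table 2): T. Cognitive ability section: T0 and T2.
- Allocation (Randomization section): participants are assigned in the order in which they finish walking practice, so T0 falls before the combined treatment.

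**Changes each schedule allows**

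| Scores | Visits with data | Changes from BL | Changes from T0 |
|---|---|---|---|
| SCATS, NPRS, NBDS, NBSS | BL, T0, T1, T2, F1, F4, F8 | 6 | 5 |
| CVLT3, O-TMT, Table 2 read as every T visit | T0, T1, T2 | 0 | 2 |
| CVLT3, O-TMT, Cognitive ability section | T0, T2 | 0 | 1 |

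Under either reading the number of changes from BL is 0 for the two cognitive tests.

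**What the Friedman analysis does with one change per person**

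The Friedman statistic for n persons and k repeated values, with rank sums R_j, is

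12 / [n k (k + 1)] × Σ R_j² − 3 n (k + 1), on k − 1 degrees of freedom.

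With only T2 minus T0, k = 1. Each person's single value has rank 1, so R_1 = n, and the statistic is

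12 / (2n) × n² − 6n = 6n − 6n = 0, on 1 − 1 = 0 degrees of freedom.

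It is zero whatever the data are. As a practical check, scipy's Friedman routine was run with 16 simulated persons. It refused one column and two columns, asking for at least three, and ran with three.

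**What remains usable**

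T2 minus T0 brackets the combined treatment, and all three arms are scheduled for it. Only Placebo + WALK_tSTIM receives no hypoxia. Setting tAIH + WALK_tSTIM against it varies the breathing intervention and holds stimulation constant.

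**The case against.** The strongest reply is that baseline can sensibly be taken as T0 for these two tests. T0 is the last measurement before the combined treatment, it leaves out the two weeks of walking practice, and Hypothesis 1 already uses the end-of-practice assessment as a reference. That stands as an argument for T0 as the right reference. It does not rescue the text. The same sentence covers four scores that are collected at BL, so one word would mean two visits within one analysis. Where Hypothesis 1 means the end-of-practice assessment, it says so. Even with T0 granted, a single change does not fit a repeated-measures analysis over time.

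A reader might go further than the documents allow in four ways.

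- *The cognitive safety result is lost.* It is not: T0 and T2 give a usable before-and-after comparison between groups.
- *Table 2 and the text contradict each other, so the two sites will test different numbers of times.* T is a generic code that is not split by visit for any measure, and the Cognitive ability section can be read as narrowing it to T0 and T2. The article also describes protocol training and regular checks of assessment logs. The entry is loose, but divergent testing is conjecture.
- *Practice on repeated testing will hide a decline.* The documents give no size for a practice effect, and Hypothesis 3 already includes a comparison between groups, which is the comparison that would guard against it.
- *Leaving the tests out of the follow-ups is an error.* Hypothesis 3 promises no result on persistence of cognitive change. The absence of testing at F1, F4 and F8 is a design limit to acknowledge and contradicts nothing stated.

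It might also be said that the full analysis plan would settle this. It can choose a method, but it cannot analyse a BL score that is not scheduled, and the article itself states the conflicting reference and schedule.

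**Conclusion.** The point holds in a limited form. For two of the six scores in Hypothesis 3, the stated analysis cannot be applied as worded: there are 0 changes from BL, and 1 change from T0 under the schedule in the Cognitive ability section (2 if Table 2 is taken to include T1). The other four scores have a BL value and are not affected. The cognitive comparison is recoverable from T0 and T2, so this is an analysis to restate and not a missing endpoint. It should be corrected before analysis, because it belongs to the safety aim and the correction is nearly free.

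The conclusion rests on reading BL and T0 as different visits, as the Figure 3 caption and the Table 2 legend both do, and on T0 preceding the combined treatment, which follows from the visit timing and the allocation rule.

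**What to change.** 1. In Hypothesis 3, state that T0 (after walking practice, before the combined treatment) is the reference for CVLT3 and O-TMT.
2. For these two scores, replace the Friedman analysis with a between-group comparison of the T2 score adjusted for T0, or a rank-based equivalent. Name tAIH + WALK_tSTIM versus Placebo + WALK_tSTIM as the main contrast for hypoxia, and report the tAIH + WALK_tSHAM arm as well, since it also receives hypoxia.
3. In Table 2, change the entry for both tests from T to T0, T2, to match the Cognitive ability section.
4. Acknowledge under Study limitations that cognition is not measured after T2.

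The cost is a few sentences and one table correction. No test, visit or participant burden is added. Retesting only those whose T2 score fell is not recommended: it adds assessments that Hypothesis 3 does not need, and selecting on a low score invites regression to the mean, which would make any apparent recovery hard to interpret.

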### Experiment protocol

We developed a study protocol to measure the extent to which tAIH priming boosts the efficacy and potency of training-related functional gains in persons with chronic SCI (Fig. 1). Study participants enroll in 23 intervention and assessment sessions at one of the two clinical trial sites (Fig. 3). Physical therapists serve as trainers and raters; they complete competency and protocol training before their study involvement to ensure rater and training reliability within and between the clinical sites. The interventions consist of eight sessions of walking practice followed by eight combinatorial treatment sessions (four sessions per week for 4 consecutive weeks).

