**FIG. 3. f3:**
[figure not shown]
Timeline of interventions and assessments. After the initial screening visit (S), each intervention consists of eight sessions of walking training (WALK) alone, followed by eight additional sessions of tAIH or Placebo before WALK_tSTIM_ or WALK_tSHAM_. Assessments occur at baseline (BL), at the end of intervention weeks 2 (T_0_), 3 (T_1_), and 4 (T_2_), and, again, after 1 (F_1_), 4 (F_4_), and 8 weeks (F_8_) after the last intervention session. tAIH, therapeutic intermittent hypoxia; WALK_tSTIM_, transcutaneous spinal stimulation-enhanced walking therapy.

We anticipate that tAIH before WALK_tSTIM_ will exceed the benefits of walking practice (WALK), tAIH + WALK_tSHAM_, or Placebo + WALK_tSTIM_ on enhancing the performance of the trained task of overground walking. Justification for the treatment sequence of tAIH followed by WALK_tSTIM_ is based on the estimated time (minutes) required for tAIH to facilitate expression of BDNF.^27^ Applying tAIH ∼1 h before WALK_tSTIM_ may promote temporal alignment of mechanisms of WALK_tSTIM_ neuromodulation with complementary mechanisms of tAIH-induced plasticity that involve BDNF. Details on these interventions are below.

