#### Walking practice

Participants receive eight 45-min WALK sessions over 2 consecutive weeks. The WALK sessions consist of intensive walking-related functional tasks using a skill-based training approach.^6^ The training includes activities related to walking speed (10MWT), initiation and balance (TUG), and walking endurance (6MWT). Recent studies found that skill-based walking practice is more consistent with community walking, providing meaningful gains in walking function after neurological injury.^28–31^ Walking practice emphasizes learning sensorimotor skills for community walking, including walking speed, endurance, stepping balance, and initiation.^30^ Participants may rest up to 15 min during the practice sessions. During the WALK sessions, the physical therapist trainer will provide physical assistance as needed for safety. Step count, peripheral blood oxygen saturation (SpO_2_), heart rate (HR), and blood pressure (BP) are measured at each session.

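### Hypothesis 3 judges within-arm safety against a baseline taken before the walking run-in, so run-in change is mixed with treatment-period change; T0 should be named as the reference visit

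*Protocol article*

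**What the plan says.** All places are in the Protocol article.

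- **Statistical analysis, Hypothesis 3.** The prediction is within-arm: "We predict no difference in SCATS, NPRS, CVLT, O-TMT, NBDS, and NBSS scores after daily tAIH + WALK_tSTIM_ compared to baseline". The analysis variable follows: "Changes in these scores relative to baseline are the repeated measures". A Friedman analysis by ranks is then used "to compare these relative scores between and within groups". Hypertension and autonomic dysreflexia are handled separately, by relative risk between interventions.
- **Experiment protocol and Fig. 3 legend.** "The interventions consist of eight sessions of walking practice followed by eight combinatorial treatment sessions". The visits are listed in order: "Assessments occur at baseline (BL), at the end of intervention weeks 2 (T_0_), 3 (T_1_), and 4 (T_2" and then the follow-ups F1, F4 and F8.
- **Walking practice.** "Participants receive eight 45-min WALK sessions over 2 consecutive weeks".
- **Table 2.** SCATS, NPRS, NBDS and NBSS are scheduled at B, T and F. The key separates B from T: "S = screening day; B = baseline; T = testing session; F = follow-up (1, 4, and 8 weeks); I = intervention day". CVLT and O-TMT are scheduled at T only.
- **Cognitive ability.** "We will assess cognitive function after the last walking practice session and after the last intervention session", that is, T0 and T2.
- **Hypothesis 1.** It first speaks of change from baseline assessments, but then names the assessment at the end of walking practice as the reference for the comparisons at T1, T2 and follow-up. Hypothesis 3 has no such sentence.

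**The concern.** The safety claim is about tAIH combined with stimulated walking. Its stated within-arm test, for four of the six scores, starts two weeks before either treatment is given. Those two weeks hold eight 45-minute sessions of demanding walking practice, and the Adverse event reporting section itself lists pain and soreness after training among the events to record. A pre-practice reference therefore charges any run-in effect to the combination.

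The direction matters because the prediction is one of no difference. If practice eases a symptom and the combination then worsens it by a similar amount, the change from baseline is near zero and reads as support for safety. If practice alone causes soreness that persists, it reads as harm from the combination.

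The term baseline also does two jobs in one sentence. For four scores it points to BL. For the two cognitive scores no BL value is scheduled, so it can only mean T0.

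**Working it through.** The protocol gives no power, SD or margin for Hypothesis 3, so there is no figure of its own to reproduce.

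**1. Is BL a different visit from T0?** Walking sessions 8 + treatment sessions 8 = 16. Assessments BL, T0, T1, T2, F1, F4, F8 = 7. 16 + 7 = 23, which is the session count given under Experiment protocol. BL is therefore a visit of its own, listed before the week-2 assessment, and Table 2 gives the four scores at both.

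**2. What each change measures.** Let r be the mean run-in change (BL to T0) and h the mean change over the treatment period (T0 to T2), with positive values meaning worse.
- Expected change from BL to T2 = r + h.
- Expected change from T0 to T2 = h.
- If r = -h, the BL-referenced change is zero and the worsening is hidden.
- If h = 0 and r > 0, the BL-referenced change is r and harm is mimicked.

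**3. Between arms.** Under Randomization, participants are assigned in the order in which they finish walking practice, so r has the same expectation in every arm. For arms A and B, (r + h_A) - (r + h_B) = h_A - h_B, with either reference. A simulation (20,000 runs, 16 per arm, assumed correlation 0.7 between visits) agrees: with h = 0.5 SD in one arm and 0 in the other, the mean contrast is 0.50 SD from BL and from T0, and with h = 0 in both about 5% of trials reject.

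**4. Within-arm size on the NPRS (illustrative).** Paired t-test, n = 16 (completers per group, Sample size section), two-sided 0.05, shift 1.0 point. The SD of the change is assumed. Noncentrality = shift / (SD / √16).

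| SD of change | Noncentrality | Detected |
|---|---|---|
| 1.0 | 4.00 | 96% |
| 1.5 | 2.67 | 70% |
| 2.0 | 2.00 | 46% |

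This is the detection rate for a 1.0-point harm from T0. With r = -1.0 the shift from BL is 0 and detection is 5%. With h = 0 and r = +1.0, change is declared from BL at the rates in the table.

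**5. Smaller run-in shifts (illustrative).** Same simulation as step 3, in SD units of the score; SD of change = √(2 × (1 - 0.7)) = 0.775.

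| r | h | Rejected, BL reference | Rejected, T0 reference |
|---|---|---|---|
| +0.3 | 0 | 31% | about 5% |
| +0.5 | 0 | 67% | about 5% |
| -0.3 | 0.5 | 17% | 68% |
| -0.5 | 0.5 | 5% | 68% |

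**6. The rank test actually named.** Friedman ranks visits within a participant. Subtracting one constant per participant, whether the BL or the T0 value, leaves those ranks unchanged. What counts is which visit enters as the comparator. In a simulated Friedman test with an assumed 0.5 SD harm cancelled by the run-in, rejection was about 5% with BL as the comparator visit and about 60% with T0.

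**The case against.** Several replies have force.

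- **Arms are also compared with each other.** This stands. A reader might infer that the whole Hypothesis 3 analysis is biased. The documents do not support that: assignment follows the run-in, so between-arm contrasts are unbiased with either reference, and hypertension and autonomic dysreflexia are compared between interventions. The within-arm problem remains, because the written prediction is within-arm. Every arm also receives tAIH, stimulation or both, so no between-arm contrast sets the combination against walking practice alone.
- **T0 may already be in the model.** A reader might infer that the T0 values go unused. The text does not say so. Time is a factor, T0 is a testing visit, and (T2 - BL) - (T0 - BL) = T2 - T0. But the text does not name that contrast, while it does name baseline.
- **Baseline may have been meant as T0.** This is possible, since for CVLT and O-TMT it can mean nothing else. For the other four scores an analyst following Table 2 would take B.
- **The t-test figures do not model a Friedman test.** This is correct as to the reference subtracted (step 6). The detection rates show the mechanism and are not a property of this plan. The run-in shifts are assumed, exact cancellation is a chosen worst case, and the protocol supports possible soreness but nowhere states that practice reduces pain.
- **T0 is not a clean reference.** This also stands. The treatment weeks contain eight further walking sessions, so change from T0 still carries practice and time effects, and transient soreness at T0 could raise the reference and mask later worsening. BL is a fair reference for the safety of the whole programme.

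**Conclusion.** The point holds for the within-arm comparison of SCATS, NPRS, NBDS and NBSS. As written, that comparison uses a visit before the walking run-in, mixes run-in change with treatment-period change, and can hide or mimic harm from tAIH + WALK_tSTIM. It does not extend to the between-arm contrasts, to hypertension and autonomic dysreflexia, or to the cognitive tests, whose only pre-treatment value is T0.

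The size cannot be taken from the documents. The figures of 70% against 5%, and the range around them, rest on an assumed SD, an assumed correlation and an assumed run-in shift. If the run-in leaves these scores unchanged on average, the two references have the same expected within-arm change. This is a change that should be made, because it affects how a safety statement is read and needs only wording.

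**What to change.** In Statistical analysis, Hypothesis 3:

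1. Name T0 as the reference visit for all scores, as Hypothesis 1 does for the walking tests. Compare T1, T2, F1, F4 and F8 with T0 for SCATS, NPRS, NBDS and NBSS, and T2 with T0 for CVLT and O-TMT.
2. Rest the safety statement mainly on the difference in change from T0 between tAIH + WALK_tSTIM and each other arm, with 95% CIs. This also removes practice and time effects shared by the arms.
3. Report BL-to-T0 change separately, as the run-in effect.
4. Keep change from BL for the four scores as a supporting display, so that an elevated T0 value would be visible.

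The cost is a few sentences of analysis text and one extra display. The values are already scheduled, and no visit, assessment or sample size changes. The remaining limit to state is that within-arm change from T0 is not a pure treatment effect.
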